### Confounders

Possible confounding variables are comorbid disorders and medication usage.

Comorbid disorders such as diabetes and depression are taken into account. The diagnosis is retrieved from the medical status and classified according to the Dutch translation of the Long-Term Care Facility Resident Assessment Instrument (RAI) [32]. There are eight categories; endocrine/metabolic/nutritional; cardiovascular; locomotor system; neurology; sensory; psychiatric/mood; respiratory; other (e.g., allergies, anemia, cancer, and renal failure).

Medication usage is tracked by checking the current medical list provided by the local pharmacist at every assessment interval. Coding is done according to the Dutch Pharmacotherapeutic Compass 2011 [33].

### Intervention

The intended goal of the intervention is to increase masticatory activity and ultimately, QoL. Therefore, the basic conditions to enable mastication have to be met; one has to have a healthy mouth and must be given food that requires chewing. This results in an intervention aimed at improving oral health care and increasing food consistency.

Oral health care comprises brushing the teeth at least once a day, for at least one minute per jaw. This is a minimum requirement, brushing the teeth twice daily is recommended, in combination with the use of toothpicks and dental floss. Clinical lessons are offered to train the nursing staff in providing this oral health care. Instructions on how to care for a dental prosthesis is also topic of these lessons. The specific skills needed for providing oral health care are also practiced. This is in concordance with the 2007 ‘Guideline oral health care in (residential) care homes for elderly people’ [34].

Increasing food consistency is achieved by: a) evaluation of the need for pureed foods and b) offering food of tougher consistency. Due to apraxia (i.e. inability to perform tasks or movements) or dysphagia (i.e. difficulty in swallowing), some participants are not able to chew and swallow food of normal consistency; hence, their food needs to be pureed. However, some participants might be given pureed foods without medical need, for example out of convenience for the nursing staff. A qualified speech therapist can diagnose swallowing disorders and therefore the need for pureed food. Participants who are given pureed food without medical need will be reintroduced to more solid foods. All participants able to masticate normally are offered food of tougher consistency, such as apples, bread including its crust, crunchy cookies, raw vegetables and salads.

### Outcome variables

#### Quality of Life

The primary outcome variable is QoL, assessed with the Qualidem questionnaire [35]. The Qualidem is considered the preferred instrument [36] for rating QoL for elderly persons with dementia and is appropriate for large and small-scale settings [37]. A proxy is asked to rate observable behaviors on a 4-point Likert scale (i.e. ‘never’, ‘rarely’, ‘sometimes’, and ‘often’). Statements are for example: ‘is cheerful’, ‘refuses food’, ‘smiles’, or ‘wants to stay in bed’. For each statement, 0, 1, 2 or 3 points are awarded. The most positive outcome is given the highest point value (e.g., ‘smiles often’ is given 3 points, ‘refuses food often’ is given 0 points). A higher score suggests a higher QoL. The Qualidem score can be divided into several subscales. Not all subscales are appropriate for participants with severe dementia, so only the four subscales recommended for this group [38] will be included; ‘care relationship’ (0-21 points), ‘positive affect’ (0-18 points), ‘restless tense behavior’ (0-9 points), and ‘social isolation’ (0-9 points). The maximal score is 57 points.

As described earlier, QoL comprises many aspects of life. In order to assess this multicomponent aspect of QoL, the following secondary outcome variables are included.

#### Cognition

Cognition, especially memory and executive function, is investigated using a pen-and-paper-based neuropsychological assessment. Trained examiners, blind for the intervention, will visit the participants at the care unit. First, the participant is screened with the MMSE. Based on the MMSE score, a set of neuropsychological tests will be conducted. If a participant is not able to give a single adequate response on any of the MMSE questions (i.e. MMSE score is zero) no further cognitive testing will take place. Participants scoring 1-4 on the MMSE will take the first four tests described below, and participants scoring 5 or higher on the MMSE will perform these tests and three additional tests (also described below). All these tasks are complementary as they assess different cognitive skills.

#### Category fluency

Category fluency is assessed in two separate instances, by asking the participant to name either as many animals or as many professions as possible in one minute [39,40]. Time is measured with a stopwatch, and all responses are recorded. Identical responses are counted only once (e.g., horse, horse; doctor, doctor), responses assigning gender (e.g., lion, lioness; steward, stewardess) are counted as two correct responses. These rules are explained to the participant before starting. Faulty responses are ignored (i.e. not counted nor subtracted). If the participant starts a random conversation or remains quiet, a gentle reminder (‘can you name any other animals/professions?’) is given. The obtained score is the amount of correct responses.

#### Memory and attention

Memory and attention are assessed by verbally presenting sequences of numbers to the participant, who has to repeat them [41]. The sequences start out with a length of two digits, and after three items, one extra digit is added. The task is cut off when two out of three responses are incorrect. Only correct responses are counted; faulty responses are ignored. The participant is allowed to make corrections. Maximal score is 21.

#### Working memory

Working memory is assessed with a digit span backwards task, which is virtually the same as above; only this time the participant has to give the response in the reverse order [41]. New sequences of digits are used. The task is cut off when two out of three responses are incorrect. Only correct responses are counted; faulty responses are ignored. The participant is allowed to make corrections. Maximal score is 21.

#### Visuospatial function

In order to assess visuospatial function, incomplete line drawings are shown, while the participant has to indicate what the images represent [39]. The drawings are of increasing difficulty, showing animals or everyday items or situations (e.g., a fish, a book, or a man carrying something heavy). After five incorrect responses, the task is cut off. In case of incomplete responses (e.g., ‘a man’ instead of ‘a man carrying something heavy’), the examiner asks the participant to elaborate: ‘please describe everything you see’. Only correct responses are counted; faulty responses are ignored. The participant is allowed to make corrections. Maximal score is 20. If a participant scores 5 points or higher on the MMSE, three tests are added:

#### Verbal long term memory

To assess verbal long term memory, the examiner reads out loud a list of eight everyday words (such as ‘pencil’ or ‘bird’), which the participant must repeat from memory after each presentation; this is repeated five times [42]. Points are awarded for correct responses; the maximal score is 40. After approximately 10 minutes, a delayed free recall and recognition condition will be administered. During the recognition condition, the participant has to indicate whether a word does or does not belong to the original list. Sixteen words are now read out loud, the eight original words and eight new words. Maximal score for free recall is 8, maximal score for recognition is 16.

#### Nonverbal episodic memory

A visual memory task is used to measure nonverbal episodic memory [41]. A card with eight red squares printed on it is placed between the examiner and the participant. The examiner taps the squares in a certain order which the participant is asked to repeat. The sequences start with a length of two squares and after two trials the sequences are lengthened with square. The task is cut off when both responses of a certain length are incorrect. Only correct responses are counted; faulty responses are ignored. The participant is allowed to make corrections. Maximal score is 14.

#### Nonverbal working memory

By using virtually the same task as above, nonverbal working memory is assessed [41]. This time the participant is asked to give the response in the reverse order, the printed squares are colored green and new sequences are used. The task is cut off when both responses of a certain length are incorrect. Only correct responses are counted; faulty responses are ignored. The participant is allowed to make corrections. Maximal score is 14.

#### Assessment of mood

Mood is assessed with two questionnaires regarding observable behaviors, measuring either depression or agitation. Both questionnaires will be filled out by a proxy, typically a member of the permanent nursing staff.

#### Depression

The presence or absence of depression is qualified using the Cornell Scale for Depression in Dementia (CSDD; [43] Dutch version (CSDD-D; [44]. Nineteen statements about the participant are scored on a Likert scale: a = not able to judge; 0 = absent; 1 = slightly or variably present; and 2 = severe. Maximal score is 38 points; a higher score indicates the presence of more depressed behaviors. Statements refer to behaviors such as suicidal tendencies and facial expressions of sadness or fear, but also to weight loss or sleep disturbances. A score below 8 is considered to be within the normal range and a score of 8 and higher is indicative of depression [43,45].

#### Agitation

The amount of agitated behaviors is scored using the Dutch version of the Cohen-Mansfield Agitation Inventory (CMAI) [46]. A total of 29 observable behaviors are scored on a 7-point Likert scale. Items are behaviors such as spitting, (verbal) aggression, biting, screaming, complaining, and others. The behaviors can be observed never (1), less than once a week (2), once or twice a month (3), several times per week (4), once or twice per day (5), several times per day (6), or several times per hour (7). Minimal score is 29; maximal score is 203. A higher score is indicative of more agitated behaviors.

#### Assessment of independence

The ability to perform activities of daily living is assessed with the Katz index of Independence in Activities of Daily Living [47]. This index rates five activities and the ability to perform them unaided. They are: dressing, using the toilet, eating, moving around, and taking a shower or bath. A sixth question regards whether the participant is incontinent. A score of 1 indicates independence, score 2 stands for ‘needs some help’, and a score of 3 is given when someone is completely dependent (or, completely incontinent). Minimal score is 6; maximal score is 18.

#### Assessment of the rest-activity rhythm

The rest-activity rhythm is a circadian rhythm that reflects the sleep-wake rhythm in an indirect way. The rest-activity rhythm is measured during a week (7*24 hours), using an Actiwatch activity monitor (Cambridge Neurotechnology Ltd., Cambridge, United Kingdom). The Actiwatch is a small device that is worn on the wrist. It is placed on the dominant arm, unless this leads to agitation (e.g., due to presence of a wristwatch or bracelet). The Actiwatch is taken off only during showering since it is not waterproof. The Actiwatch records the motions of the arm, which are a proxy for overall activity [48]. The recorded data are analyzed for the following variables:

#### Interdaily stability (IS)

The interdaily stability is a measure for the degree of similarity of activity patterns within the measured period. A stable rhythm is characterized by a higher IS score; scores are between zero and 1.

#### Intradaily variability (IV)

The intradaily variability is the difference in activity levels in periods throughout the day. A normal activity pattern shows low IV; a sinusoid pattern results in a score of zero, a score of 2 is obtained for noise, and higher scores can arise obtained due to peaks in activity.

#### Relative amplitude (RA)

The relative amplitude is calculated by dividing the difference between the means of the ten most active hours (M10) and the five least active hours (L5) by the sum of these means within a day/night cycle.

$$\mathrm{RA}=\frac{M10-L5}{M10+L5}$$

A larger RA is associated with a more pronounced wake/sleep cycle. A more detailed description of these variables and their analysis is available elsewhere [48].

#### Assessment of blood pressure

Blood pressure is measured in millimeters of mercury (mmHg) with a blood pressure monitoring device (SpaceLabs Medical Inc., Redmond, Washington, United States of America). The participant is sitting down quietly, unless they are bedridden in which case they are lying down. Systolic blood pressure and diastolic blood pressure are noted, as well as heart rate. Hypertension is defined as systolic blood pressure higher than 160 mmHg and/or diastolic blood pressure over 95 mmHg [49].

#### Assessment of masticatory function

Mastication can be assessed in several ways. Most notably is the distinction between subjective, self-rated masticatory ability and the objective outcome masticatory efficiency (also described as masticatory performance) [50,51]. In the present study, masticatory ability is not assessed, since the cognitively impaired participants are not likely to be able to reliably answer questions about their chewing capacity. Participants’ masticatory efficiency is assessed using several techniques. First of all, the dental status is recorded: is the participant dentate, is he/she wearing a partial of full prosthesis, etc. If possible, the dental records are used for obtaining this information, otherwise, nursing staff is interviewed, or a visual inspection is performed. Secondly, several assessments are taken:

#### Occluding units

The number of pairs of upper and lower teeth that touch each other when the mouth is closed (i.e. occluding units) are measured using dental modeling wax (Alminax; Müller & Weygandt, Büdingen, Germany). The wax is solid at room temperature and becomes soft when immersed in warm water. The participant bites down on a plate of softened wax and then it is allowed to harden again. Determination of the number of occluding units is done by visual inspection. In complete dentitions, 8 teeth are present in each quadrant (two incisors, one canine, two premolars, and three molars). Thus, the maximal score is 16 occluding units (i.e. 32 teeth).

#### Maximal mandibular excursions

Active, voluntary, mandibular mobility is assessed as the distance between the upper and lower incisal edges, in millimeters, and is measured with a flexible plastic ruler (Dental Union, Nieuwegein, The Netherlands) [30,52]. First, the participant is asked to open his/her mouth as wide as possible without experiencing any pain. Next, the participant is encouraged to open his/her mouth as far as possible, even if this is painful, thus enabling the assessment of the maximal mouth opening. During the maximal opening, the participant is continuously encouraged. Maximal protrusion (i.e. outward forward movement of the mandible) is assessed by asking the participant to push the lower jaw forward as far as possible. Laterotrusion (i.e. outward movement of the jaw to the side) to the left and right are also measured. After every mandibular excursion, the participant is asked whether this is painful and if so, where the pain is located and what the intensity of the pain is. Pain location is recorded as joint area, pre-auricular, cheek area, floor of the mouth, temporal area, and other. Pain intensity is recorded on a 5-point Likert scale: 0 = no pain, 1 = tenderness, 2 = mild pain, 3 = moderate pain, and 4 = severe pain. Overjet (i.e. the antero-posterior distance between the upper and lower incisors), overbite (i.e. the vertical overlap of the upper and lower incisors), and midline deviation (i.e. the horizontal distance between the upper and lower dental arch midlines) are recorded while the participant rests in occlusion. The vertical maximal opening is corrected for overbite, the protrusion is corrected for the overjet, and the laterotrusions are corrected for the midline deviation.

#### Maximal voluntary bite force (MVBF)

The maximal voluntary bite force (MVBF) is measured with the VU University Bite Force Gauge (VU-BFG). The VU-BFG is a hand-held device which uses a load cell to measure maximal voluntary bite force in kilograms. The VU-BFG can be used centrally between the incisors or unilaterally between the (pre-) molars. For this study, the VU-BFG will be used between the incisors. The participant is instructed to bite as long and hard as possible and is encouraged continuously during the sampling. If the sampling fails (e.g., due to losing the prosthesis), a second attempt will be made after a rest period. Maximal sampling time is 20 seconds, and sampling takes place at a frequency of 50 Hz. All bite force samples are logged; the highest (i.e. peak) value is used as MVBF.

#### Mixing ability

In order to quantify actual masticatory performance, a mixing ability test in which the participant has to orally knead two viscoelastic colored materials [53,54] is used. A four-gram sample made of blue and pink chewing gum (Bubblicious® Ultimate Original and Twisted Tornado; Cadbury, London, United Kingdom) is given to the participant, with the instruction to chew naturally. The sample resembles a piece candy due to its general appearance (bicolor capsule-shaped sample in a cellophane wrapper) and smell (sugary and sweet) which makes it easier for the participant to accept it as test food. A casting mold ensures consistent production of samples. Several protocols use a fixed number of chewing cycles, e.g. [53]. However, participants suffering from dementia may find it hard to count and chew at the same time. An observer cannot accurately distinguish individual chewing cycles either, due to for example swallowing in between chewing motions, movements of the head while chewing (e.g., looking around), presence of a tremor, or obscuring of the jaw due to facial features such as sagging skin or beard (pilot data, not shown). Using a fixed amount of chewing cycles is therefore not possible in this population. Since in healthy people the average chewing frequency is stable at approximately 1.4 hertz (1.45 Hz for women and 1.30 Hz for men; [55], the assumption is made that this is also the case in persons suffering from dementia. This was confirmed in a pilot study (data not shown) and therefore a standard chewing time of 20 seconds will be used. A stopwatch is used to measure time. After digital optical analysis, a mixing ability score is obtained [53,54].

### Statistical analysis

The data from this prospective longitudinal matched cluster randomized single-blind multicenter study will be analysed using a linear mixed model. The fixed effects are *‘condition’* and *‘time’*; the linear ‘*condition x time’* interaction is the effect parameter of interest and *‘care unit’* and *‘participant (within the care unit)’* are the random effects (both intercepts and slopes). An intention to treat analysis will be performed.

The baseline (cross-sectional) data will also be analysed for Pearson’s and/or Spearman’s coefficients, to establish correlations between the primary outcome variable QoL and the secondary outcome variables (viz., cognition, mood, independence, rest-activity rhythm, blood pressure, and masticatory function). Additionally, linear regression analyses will be performed to study the independent contribution of the various secondary outcome variables to QoL.

A baseline comparison will be performed to make sure that the intervention group and control group are similar with regards to variables that are not of primary interest (i.e. the covariates and confounders) and the outcome variables. Any difference between the groups afterwards is then likely due to the intervention. If there are differences between the groups prior to the intervention, the baseline scores will be incorporated as covariates in the analysis.

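### The baseline regressions of QoL use mood scales (CSDD, CMAI) as predictors although they rate domains that make up about 47% of the QoL score, so their coefficients cannot be read as independent contributions

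*Protocol article*

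**What the plan says.** The Statistical analysis section describes a supplementary analysis next to the primary mixed model. It starts with correlations: "The baseline (cross-sectional) data will also be analysed for Pearson’s and/or Spearman’s coefficients", between QoL and the secondary outcomes, which are listed as "viz., cognition, mood, independence, rest-activity rhythm, blood pressure, and masticatory function". It then adds that "linear regression analyses will be performed to study the independent contribution of the various secondary outcome variables to QoL".

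Three other places bear on how this can be read.

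- **Background.** QoL is defined to include mental health, with freedom from fear, agitation and mood disorder as the examples.
- **Outcome variables, Quality of Life.** The primary score is the sum of four Qualidem subscales: care relationship (0-21), positive affect (0-18), restless tense behavior (0-9) and social isolation (0-9), maximum 57. A proxy rates observable behaviour. The section closes by presenting the secondary outcomes as aspects of QoL: "In order to assess this multicomponent aspect of QoL, the following secondary outcome variables are included".
- **Assessment of mood.** Mood is covered by two questionnaires on observable behaviour, "measuring either depression or agitation", both completed by a proxy who is typically a permanent member of the nursing staff. The examples given for the CSDD include visible sadness and fear as well as weight loss and sleep problems. The CMAI counts agitated behaviours.

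The document does not acknowledge the overlap between the outcome and these predictors or say how it will be handled.

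**The concern.** A predictor contributes independently to an outcome only if it is something other than the outcome. Here the protocol counts mood and agitation as part of QoL, scores them within the Qualidem total, and then uses two further proxy ratings of the same domains to explain that total. Two consequences follow.

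1. A sizeable CSDD or CMAI coefficient is expected simply because part of the outcome is the same domain rated again, possibly by the same person. The Background itself warns that proxy ratings are influenced by the caregiver's own mood and cognition. Bite force and mixing ability are instrument-based and share no such rater effect.
2. The trial's hypothesis is that better mastication improves QoL including mood. Conditioning on mood takes out whatever part of the mastication-QoL association runs through the mood-type subscales. Set beside large mood coefficients, a small adjusted mastication coefficient could be misread as showing that mastication matters little for QoL.

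**Working it through.** **Share of the score (inputs from the Quality of Life section).** The subscale maxima reproduce the stated total: 21 + 18 + 9 + 9 = 57. Matching depression to positive affect and agitation to restless tense behavior gives (18 + 9)/57 = 27/57 = 47.4%. The matching is by domain name. Counting only restless tense behavior gives 9/57 = 15.8%; adding social isolation to the two gives 36/57 = 63.2%.

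**Set-up for the regression (all correlations and reliabilities are assumptions; the protocol gives none).** Write the score as Q = 27A + 30B. A is the mood-type part and B the rest, each with unit variance, and c is the correlation between them. This takes the spread of each part as proportional to its maximum. M is one mood scale, scored in the same direction as A, which measures A with reliability rel, so its correlation with A is √rel. X is masticatory function, correlated rA with A and rB with B.

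**Circularity of the mood coefficient.** Take the extreme case in which mood is unrelated to the rest of QoL (c = 0). Then

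corr(M, Q) = √rel × 27/√(27² + 30²) = √rel × 27/40.36 = 0.669 × √rel.

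This is 0.47 at rel = 0.5 and 0.56 at rel = 0.7. A substantial association arises although, in this case, mood tells us nothing about any other part of QoL. It does not depend on mastication at all.

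**Effect on the mastication coefficient.** From the exact two-predictor regression, the share of the unadjusted coefficient that remains once M is added is

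retained = [27rA + 30rB − rel × rA × (27 + 30c)] / [(1 − rel × rA²)(27rA + 30rB)].

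With rA = rB = 0.3, 27rA + 30rB = 17.1. Then:

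| rel | c | Calculation | Retained | Lost |
|---|---|---|---|---|
| 0.5 | 0.3 | (17.1 − 0.15 × 36)/(0.955 × 17.1) | 0.716 | 28% |
| 0.5 | 0.5 | (17.1 − 0.15 × 42)/(0.955 × 17.1) | 0.661 | 34% |
| 0.7 | 0.3 | (17.1 − 0.21 × 36)/(0.937 × 17.1) | 0.595 | 40% |
| 0.7 | 0.5 | (17.1 − 0.21 × 42)/(0.937 × 17.1) | 0.517 | 48% |

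**Sensitivity to the assumptions.**
- If rA = 0, the formula gives retained = 1, so nothing is lost whatever the overlap.
- With a mood-scale correlation with A of 0.7 (rel = 0.49), rA = 0.15 and rB = 0.3, the loss is 19% to 23%.
- With the same scale, rA = 0.3 and rB = 0, it is 64% to 75%.
- With a scale correlation of 0.9, rA = 0.3 and rB = 0, the whole coefficient is lost.

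The overlap alone therefore does not fix the size. The baseline correlation between mastication and mood does.

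**The case against.** The strongest points on the other side are these.

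- **The model is not spelled out.** The text speaks of regression analyses in the plural and fixes no predictor set. One model containing every secondary outcome is an inference. This stands as a caution, but an independent contribution implies some mutual adjustment, so mood and mastication in one model is the natural reading.
- **Mastication is one of six listed domains, not the named target.** An independent contribution is conditional by definition. This stands too. It is a reason to add a model without the mood scales, not to replace the authors' question. It does not rescue the CSDD and CMAI coefficients, whose circularity has nothing to do with mastication.
- **Shared items are not shown.** The Qualidem examples (cheerfulness, smiling, refusing food) differ from the CMAI examples (spitting, biting, screaming), and the CSDD reaches into weight and sleep. The overlap is demonstrated at the level of domain and rating method only.
- **Unadjusted correlations are planned as well**, so the marginal mastication-QoL association will be visible.

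A reader might go further and infer that the mastication effect is removed by construction, or that mastication will look unimportant whatever the truth. The document does not support that: the loss needs a baseline correlation between mastication and mood, which is not reported, and it is zero without one. A reader might also reach a loss of 48% to 68% from (1 − rel)/(1 − r² × rel) with r = 0.3, which gives 0.5/0.955 = 0.52 and 0.3/0.937 = 0.32 retained. That holds for the affect part of the score only. The planned outcome is QoL, scored as the 57-point total.

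**Conclusion.** The concern holds in a limited form. With mood counted within QoL by definition and domains matching the two mood scales supplying 27 of the 57 points, the CSDD and CMAI coefficients are partly circular and cannot carry the interpretation that the protocol gives them. This needs no assumption about mastication; it rests on matching domains by name.

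For mastication the conclusion is conditional. If it is correlated with mood at baseline, a model with CSDD or CMAI understates its total association with QoL, by about 28% to 48% of the coefficient on the total score under the values in the table. Those values are illustrative, and the loss can be nil.

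The reach is narrow. This is a supplementary cross-sectional analysis. The condition-by-time interaction, which the protocol names as the effect of interest, is untouched. It would be wrong to treat this regression as the trial's evidence for its hypothesis, since the document gives it no such role. The point is a cheap improvement that changes what this one analysis can conclude.

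**What to change.** 1. Report the regression of QoL on masticatory function both with and without CSDD and CMAI. Adjust both versions for the stated covariates (age, gender, educational level, ApoE4 status) and for comorbidity other than the psychiatric/mood category listed under Confounders; otherwise mood re-enters the model by that route.
2. Where CSDD or CMAI is a predictor, also report results by Qualidem subscale, for example with care relationship plus social isolation (21 + 9 = 30 points) as the outcome. Describe this as the less overlapping part, not as free of overlap, because the protocol gives no items for these subscales.
3. State that CSDD and CMAI coefficients for the total score will not be interpreted as independent contributions to QoL, and that a mastication coefficient adjusted for them is not its total association.

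The cost is a few extra models on data already being collected, and a narrower outcome in some of them. Design, sample size and the primary analysis do not change.

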## Methods and design

### Study design

The study has a prospective longitudinal matched cluster randomized single-blind multicenter design. Assignment to either the intervention group or the control group will take place through matched cluster randomization, on a care unit level (i.e. not on an individual level). Participants in the study will be followed for 24 weeks and will be assessed at regular intervals, viz., at baseline, six weeks, twelve weeks, and 24 weeks after baseline. A care organization enrolls two care units, in order to provide matching groups within a single care setting. One group will be a control group and receive care as usual; the other group will be an intervention group. Participants are blind to the intervention. Since receiving training and altering the daily nursing care is part of the intervention, care-givers such as the nursing staff cannot be blind for the intervention. The examiners will be blinded.

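### The baseline associations of QoL with the secondary outcomes are planned without a care-unit term, so standard errors may be understated where both variables cluster by unit (minor)

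*Protocol article*

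**What the plan says.** The Statistical analysis section of the protocol article handles the same residents in two ways.

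- **Longitudinal data.** These "will be analysed using a linear mixed model", in which care unit and participant within care unit "are the random effects (both intercepts and slopes"). The condition-by-time interaction is the effect of interest.
- **Baseline data.** "The baseline (cross-sectional) data will also be analysed for Pearson’s and/or Spearman’s coefficients", to relate QoL to cognition, mood, independence, rest-activity rhythm, blood pressure and masticatory function. In addition, "linear regression analyses will be performed to study the independent contribution of the various secondary outcome variables to QoL". Neither sentence names care unit, a random effect or a robust variance.

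The clustering comes from the design. Under Study design, allocation is "on a care unit level (i.e. not on an individual level"), and "A care organization enrolls two care units". Sample size gives 10 organisations and 10 participants per unit.

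On who does the rating: the Qualidem is completed by a proxy who is not further described. For depression and agitation, "Both questionnaires will be filled out by a proxy, typically a member of the permanent nursing staff". The Background notes that proxy ratings depend partly on the caregiver's own mood and cognition.

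**The concern.** Pearson and Spearman coefficients and linear regression, with their usual standard errors, take each resident as an independent observation. Residents of one unit share staff, routines and possibly raters, so their QoL scores may be alike, and so may their scores on some predictors. Two consequences follow if the methods are run as named.

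1. **Precision.** If both QoL and the predictor cluster by unit, the usual standard error understates the uncertainty and tests reject too often.
2. **Interpretation.** If units that score high on QoL also score low on, say, agitation, because of local care or rating habits, the pooled coefficient picks this up even when no association exists among residents of the same unit. That bears on the stated aim of finding each factor's independent contribution.

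The mood scales are the most plausible case, because predictor and outcome are both proxy ratings and may come from the same nursing team.

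**Working it through.** **Inputs from the article**
- Units: 10 organisations × 2 units = 20 (Study design; Sample size).
- Residents: 20 × 10 = 200.
- With dropout allowed for: 200 × 10/9 = 222.2, that is 223 rounded up. The article states 224, which agrees to within rounding. Then 224/20 = 11.2 residents per unit at baseline.
- ICC: not given. The total variance of 300 is not split between and within units.

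**Assumed:** ICCs of 0.1, 0.2 and 0.3 for both QoL and the predictor, and a two-sided 5% test. The article states no test level for these analyses.

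**Standard errors.** For a single predictor with no true association, and m residents per unit:

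- true variance / usual variance: D = 1 + (m − 1) × ICC(predictor) × ICC(QoL)
- actual size of a 5% test: 2 × [1 − Φ(1.96/√D)]

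| Both ICCs | D, m = 10 | √D | Size | D, m = 11.2 | √D | Size |
|---|---|---|---|---|---|---|
| 0.1 | 1 + 9 × 0.01 = 1.09 | 1.04 | 6.1% | 1 + 10.2 × 0.01 = 1.10 | 1.05 | 6.2% |
| 0.2 | 1 + 9 × 0.04 = 1.36 | 1.17 | 9.3% | 1 + 10.2 × 0.04 = 1.41 | 1.19 | 9.9% |
| 0.3 | 1 + 9 × 0.09 = 1.81 | 1.35 | 14.5% | 1 + 10.2 × 0.09 = 1.92 | 1.38 | 15.7% |

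Simulation with 20 units and 20,000 replicates per setting gave 5.8%, 9.2% and 14.3% for units of 10, and 5.9%, 9.4% and 15.1% for units of 11. A smaller simulation (4,000 replicates, units of 11) gave 6.2%, 9.4% and 15.8%. Formula and simulation agree.

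**Where the effect vanishes or reverses**
- Predictor not clustered (ICC 0) and QoL ICC 0.1 or 0.2: D = 1, and the simulated size stays at about 5%.
- Both ICCs 0.05, m = 10: √D = √(1 + 9 × 0.0025) = 1.01, simulated size 5.1%.
- Predictor varying only within units: true/usual standard error = √(1 − ICC(QoL)), that is 0.97, 0.95 and 0.89 for QoL ICCs of 0.05, 0.1 and 0.2. The usual standard error is then too large.

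**Interpretation.** If there is no association within units, but the unit effects on QoL and the predictor correlate at r, the pooled correlation is r × √(ICC(predictor) × ICC(QoL)). With assumed values r = −0.5 and both ICCs 0.2, this is −0.5 × 0.2 = −0.10. The usual standard error of a correlation at n = 200 is about 1/√200 = 0.07. The figures only illustrate the mechanism; nothing in the article fixes r.

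**The case against.** The strongest reply is that this is a condensed article. It does not say that residents are treated as independent, and the variance estimator for a supplementary analysis may be set out in a document not shown. That has some force for the regressions. It has less for the correlations, since a standard Pearson or Spearman coefficient has no place for a unit term. The article does name the unit term for the longitudinal model, and then names methods that omit it in the next paragraph.

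It can also be said that the coefficients are descriptive and that no test or interval is specified for them. That stands, so the point on precision applies to whatever tests or intervals are reported.

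Two stronger readings are tempting:

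- *All the standard errors are too small.* The documents do not support this. The inflation depends on the product of two ICCs, neither of which is given. Cognitive tests, actigraphy, blood pressure, bite force and mixing ability are measured on the resident, so the rater mechanism does not apply to them. A rater shared between QoL and mood is also an inference: nursing staff are named for the mood scales, whereas for the Qualidem the article says only that a proxy is asked, and the Background mentions relatives as well as nurses.
- *The trial result is at risk.* It is not. The condition-by-time effect comes from the mixed model, which includes care unit.

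**Conclusion.** The point holds in a limited form. The article models care unit for one analysis of these residents and names methods without it for another. If those methods are run as named, tests of associations between two clustered variables may be too liberal: a nominal 5% becomes about 6% at ICCs of 0.1, 9-10% at 0.2 and 14-16% at 0.3. Between-unit differences may also be reported as resident-level associations.

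The size rests on assumed ICCs, taken as equal for both variables, and on a single predictor with no true association. For weakly clustered predictors the effect is negligible, and for predictors that vary only within units it reverses. The analyses concerned are supplementary and non-randomised; the sample size and the randomised comparison are untouched. Severity is minor.

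**What to change.** - Fit the baseline regressions of QoL with a care-unit random intercept. Alternatively, keep linear regression with a cluster-robust variance and a small-sample correction, because there are only about 20 units.
- Base any test or interval for the correlations on a unit-adjusted method; the plain coefficients can stay as description.
- Optionally, as a sensitivity analysis, split each predictor into its within-unit part and its unit mean. This separates resident-level from unit-level association. It changes the quantity estimated, so it should supplement the main analysis and not replace it. It does not remove differences between raters within one unit.

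A care-unit term is what matches the longitudinal model, which as stated has no random effect for organisation.

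The cost is a sentence or two in the analysis plan and somewhat wider intervals for some associations. No new data are needed.
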